### 5.2. Data Collection

The performance and refusal rates will be assessed via independent and robust monitoring through independent surveys, data from the National Emergency Operations Centre (NEOC) and PPEP data for OPV coverage.

Apart from the regular data of NEOC, the project team will also collect data at baseline and endline. Two-stage cluster sampling will be adopted for the baseline and endline. The union councils (UC) will be considered as independent strata and each UC will be subdivided into 30 equal areas (clusters), the WHO 30 × 7 technique will be implemented to achieve the sample size and seven households (HHs) will be selected randomly within each cluster using an available sampling frame of the area [28]. Thus, a total of 840 interviews will be conducted, 210 from each of the four areas (two intervention and two control).

Face-to-face interviews will be conducted with eligible participants, after informed written consent is obtained, using a structured data collection instrument which will be based on household information, socio-demographics of the HHs, immunization status and polio campaign. After instrument development and before starting field activities, a pilot survey will be conducted; this exercise will be carried out in all non-targeted areas. All steps of the survey will be followed in the pilot exercise including the methodology, instruments, guidelines, etc. Revisions will be made based on the lessons learned in the pilot survey.

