### 3.2. Study Design

The study will adapt a pre/post-test quasi-experimental design with two intervention HRUCs and two control HRUCs. For each targeted intervention HRUC, a separate matched control HRUC of comparable size and location will be included. Union councils are the lowest administrative unit in Pakistan.

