### 3.8. Sample Size and Sampling Strategy

The polio program is well established, and demarcated vaccination areas are assigned to each vaccination team. Therefore, the areas allotted to the vaccination team will be considered as one cluster in the proposed study. The first intervention HRUC (Haji Mureed Goth) is divided into four wards, distributed into 11 areas that are each supervised by “area supervisors”, and has a total of 47 community health workers (CHWs) from the Polio Eradication Program, hence we will form 11 clusters in this HRUC. The second intervention HRUC (Mira-Khel) of district Bannu is divided into 10 areas, which are supervised by 10 area supervisors, and has a total of 43 polio LHWs from the Polio Eradication Program, thus 10 clusters will be formed in Bannu (Figure 2 and Figure 3).

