#### 4.2.2. Conditional–Collective–Community-Based Incentives (C3I)

The clusters which are successful in reducing vaccine refusals (SMC and PMC) will be eligible to receive incentives. The C3Is will be conditioned on improvements in vaccine acceptance and will not target individuals or be based on individual practices; rather, they will be targeted to benefit the entire community. These non-cash, need-based incentives will be decided with the consensus of community groups and aim to improve infrastructure linked to health, including drinking water and sanitation facilities, at the community level. The total cost of these incentives will be shared by the project (75%) and the community (25%) to improve ownership. The model of decision and delivery is the same as the CoMIC trial [21].

C3Is will be available for each cluster (21 clusters in two HRUCs) in the intervention clusters, provided they reduce refusals and hence increase the OPV and IPV coverage in a pre-defined period based on the usual data collected in the routine polio vaccine campaigns. We will calculate the mean SMC and PMC in the preceding three campaigns in each cluster, and to be eligible to receive incentives in two phases, each cluster will have to achieve the following targets over a one-year period:

At 5 months—30% improvement (from baseline)—30% reduction in SMC and PMC in the next two campaigns.

At 12 months—50% improvement (from baseline)—50% reduction in SMC and PMC in the last two campaigns.

These non-cash, need-based incentives will be decided with the consensus of UC committees and aim to improve infrastructure linked to health, including but not limited to water supply facilities, toilets and sanitation facilities. This unique incentive scheme will not target individuals or be based on individual practices; rather, it will benefit the community, as we will look at the improvement in the coverage of the defined cluster. Providing incentives that can improve the resource-poor environments of disadvantaged communities can help promote optimal health behaviors such as vaccination [20].

Community belonging and community-level influence can be central to behavior change at the individual level [15,20]. This strategy is formulated on the assumption that a group strategy that is beneficial, unifying and of which the whole community has ownership can be more effective in convincing individual community members.

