## 6. Statistical Analysis

The baseline characteristics of the study population will be reported as frequencies and percentages for categorical variables, and mean, standard deviation (SD) and median interquartile range (IQR) for continuous variables as appropriate. The immunization coverage will be reported overall and according to time and intervention groups. Subgroups including age, gender, maternal years of education, socio-economic status and area of residence will also be compared for immunization coverage. A difference-in-difference (DID) method will be used to estimate the impact of intervention over time. Multivariate analysis will be performed using binary logistic regression at endline to determine the impact of intervention controlling for multiple confounding factors. The analysis will be carried out in STATA version 17 [29].

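### Households are sampled, and the intervention delivered, by area, but the endline logistic model is named without any allowance for correlation within areas; for the difference-in-difference the error is conditional

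*Protocol article*

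**What the plan says.** **Sampling.** Section 5.2 states: "Two-stage cluster sampling will be adopted for the baseline and endline". UCs are the strata; "each UC will be subdivided into 30 equal areas (clusters"; and "seven households (HHs) will be selected randomly within each cluster". The resulting size is "a total of 840 interviews will be conducted, 210 from each of the four areas (two intervention and two control".

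**Level of the intervention.** Section 3.2 describes a "pre/post-test quasi-experimental design with two intervention HRUCs and two control HRUCs". Within the intervention UCs, delivery is by area-supervisor area. Section 3.8 gives 11 for Karachi ("hence we will form 11 clusters in this HRUC") and 10 for Bannu. Section 4.2.2 attaches the incentive to those units: "C3Is will be available for each cluster (21 clusters in two HRUCs) in the intervention clusters".

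**Analysis.** Section 6 names a DID for impact over time and a covariate-adjusted model "using binary logistic regression at endline to determine the impact of intervention", both in Stata 17. The article mentions no random effect, GEE, robust or survey variance, ICC or design effect.

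**The concern.** Binary logistic regression with its default variance assumes independent records. The survey takes seven neighbouring households at a time, and groups of households share the same mobilisation and the same collective reward. The protocol's own theory (sections 1, 2 and 4.2.2) is that belonging to a community and being influenced by it drive individual behaviour, so an ICC of zero would contradict the reasoning behind the intervention. Adjusting for confounders does not repair the variance.

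At stake are confidence intervals that are too narrow, and a false-positive rate above nominal, in the survey-based evaluation of a model that the sponsor hopes government will adopt.

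**Working it through.** **Inputs.** Households per survey area m = 7, 30 areas per UC and 4 UCs (section 5.2). Not in the document and therefore assumed: a two-sided 5% test; an area ICC of 0.05 to 0.20; areas treated as random.

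**The plan's own figure.** 30 × 7 = 210 per UC and 4 × 210 = 840, which matches. There is no power calculation to reproduce.

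**Endline logistic model.** DEFF = 1 + (m − 1) × ICC. The naive standard error is too small by 1 − 1/√DEFF. The actual type I error is 2 × [1 − Φ(1.96/√DEFF)]. The effective sample is 840/DEFF.

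| Assumed ICC | DEFF | Naive SE too small by | Actual type I error | Effective N of 840 |
|---|---|---|---|---|
| 0.05 | 1 + 6 × 0.05 = 1.30 | 12% | 8.6% | 646 |
| 0.10 | 1 + 6 × 0.10 = 1.60 | 21% | 12.1% | 525 |
| 0.20 | 1 + 6 × 0.20 = 2.20 | 33% | 18.6% | 382 |

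**Simulation check.** Layout 4 × 30 × 7, arm and site terms, an assumed 15% outcome rate, no true effect, 1,500 runs. Ordinary logistic regression rejected in 4.8% of runs at ICC 0, 8.1% at 0.05, 12.2% at 0.10 and 18.1% at 0.20. Clustering the variance on the 120 survey areas brought this back to between 5% and 6%.

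**DID.** Let r be the correlation of an area's effect between rounds. Then DEFF = 1 + (m − 1) × ICC − m × ICC × r. At ICC 0.10 this is 1.60 − 0.70r:

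| r | DEFF | Actual type I error |
|---|---|---|
| 0 | 1.60 | 12.1% |
| 0.5 | 1.25 | 8.0% |
| 0.8 | 1.04 | 5.5% |
| 1 | 0.90 | 3.9% |

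The article does not say whether the same areas are surveyed in both rounds, so r cannot be narrowed.

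**What area clustering does not cure.** In the same simulation with an area ICC of 0.10, a small UC-level ICC of 0.005 or 0.01 was added. The ordinary model then rejected in 22% or 32% of runs, and the area-clustered model still in 13% or 21%. A test based on the four UCs would have about 2 degrees of freedom (critical t 4.30), or 1 on the matched pairs (12.7).

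**The case against.** **Section 6 is silent; it does not say that clustering is ignored.** This is true. Stata's logistic regression can take a cluster-robust or survey variance, and an unseen analysis plan may specify one. A reader might infer that the sponsor has decided against adjustment, and the text does not support that. What remains is that the article names a sampling design and names an impact model, and the model as named does not fit the design.

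**Every area is sampled.** If a UC is cut into 30 areas and all 30 are visited, areas act as strata for describing these four UCs, and the design effect would be roughly 1 − ICC, below 1. This stands as a condition: the range 1.3 to 2.2 holds only when areas are treated as random. That is the relevant view for a claim about an intervention meant to be replicated elsewhere, and section 5.2 itself calls the areas clusters in a two-stage sample.

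**The survey may not carry the whole evaluation.** The outcomes in section 3.6 are refusals among missed children, and programme data are also collected. Section 6 does not tie the DID to the interviews. A covariate-adjusted logistic model does, however, need individual records, and the survey is the source of such records that the article describes.

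**Stronger readings that do not hold.**
- *Survey areas cannot be linked to delivery areas because 30 does not divide by 11.* They can nest unevenly (8 × 3 + 3 × 2 = 30), 10 divides 30 exactly in Bannu, and vaccination areas are demarcated, so a household can be assigned to one whatever the survey boundaries.
- *Selection probabilities are unequal.* If the equal areas are equal in households, seven per area is self-weighting.
- *Type I error is 16% to 38% at supervisor-area level* (m = 210/11 = 19.1 or 210/10 = 21, DEFF 1.9 to 5.0). This carries ICCs assumed for small areas over to areas about three times larger, and no count of supervisor areas is given for the control UCs.

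**Conclusion.** The point holds for the endline logistic model. As named, it understates the standard error for any positive area ICC. At an assumed ICC of 0.05 to 0.20, with areas random, the understatement is 12% to 33% and a nominal 5% test rejects about 9% to 19% of the time. The mechanism follows from the document, but the size rests on the assumed ICC.

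For the DID the point is conditional. A reader might infer that its standard errors are too small as well. That is so when area effects change between rounds, but the error is negligible at high stability and reverses as r approaches 1.

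Nor should a reader infer that area clustering makes the inference fully valid. Allocation is two UCs against two, and even a UC-level ICC of 0.005 to 0.01 leaves the area-clustered test rejecting in 13% to 21% of runs. The correction is necessary but not sufficient, and that limit has to be stated with it.

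**What to change.** Amend section 6 as follows.

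1. Fit both the endline logistic model and the DID with site terms (Karachi, Bannu) and variance clustered on area. The area may be the survey area, or the area-supervisor area if its identifier is recorded for every household in all four UCs.
2. If supervisor areas are used, add a small-sample correction such as a wild cluster bootstrap. There are 21 in the intervention arm; roughly 20 in the control arm is an assumption.
3. State whether the same areas are surveyed in both rounds. If they are, cluster the DID on area across rounds so that the between-round correlation is taken into account.
4. Report the estimated ICC and design effect, and do not report unclustered p-values.
5. State that with two UCs per arm, UC-level variation cannot be separated from the intervention effect, so p-values and confidence intervals are conditional on these four UCs.

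The cost is revised wording, a stored area identifier, a slightly longer analysis and wider confidence intervals. No extra interviews are needed.

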### 5.3. Quality Assurance

All the data will be collected electronically, and the data collection application will be developed in the local language Urdu. Handheld devices running the Android operating system will be used. Java will be used to develop a customized data collection application. MySQL databases will be used at the backend for data storage. This is a popular relational database system that provides efficient storage, retrieval and management of structured data. The data will be exported to statistical software for analysis. The application will have built-in data quality checking features to identify any missing information, inconsistencies, outliers or other errors in real time. The user will be prompted for any such errors at the time of data collection to ensure quality data. Additional validation checks will be performed at the central data repository. Data will be transferred from each handheld device at the end of the day. An institutional server will be used as per IT policy for data hosting and archiving; therefore, data will be transmitted directly to the AKU server via the internet.

In the case that internet is not available at remote locations, the team leaders will manually export a copy of the data to a memory stick to avoid any data loss.

The data collection application will be password-protected. Once a record is saved, it will not be editable by the collection staff. Data stored on handheld devices, as well as during data transfer, will be encrypted and anonymized to avoid any breach of confidentiality of participants’ personal information. Data will be archived and will be stored in a data repository at the AKU. Access to the data repository will be limited to only data management personnel directly involved in the project through their AKU-LAN identification. Once the data are transferred to the main server at AKU, it will be accessible only to the data management personnel involved in the survey. The level of access to the data will be different according to the project role of the person. The data synchronized at the AKU data repository will be replicated to a remote location as backup. The fail-over/slave server will also be maintained for restoration of the database in the event of a disaster that destroys the primary database server. A data collection application installation guide, user manual and database documentation will be created. The database documentation will include field names for all variables, their type, description, codes and value labels. Steps will be defined to transfer these data into SPSS/STATA format, retaining the variable labels and value labels.

### 5.4. Monitoring

The project activities will be regularly and rigorously monitored by the regional managers, who will be specifically trained to supervise this task. The following steps will be ensured during monitoring and quality control in the field:Each data collector will be expected to submit/sync only completed and accurate questionnaires, and every day the supervisor will check the data for completeness and timely syncing.Any discrepancies or missing data found will be resolved through discussions with the interviewers, reviewing photographs of the vaccination card (if available) or revisiting the HHs if necessary. Steps to improve the next day’s work will also be deliberated upon.District supervisors will conduct a validation process to ensure the accuracy and completeness of the collected data. They will specifically focus on verifying the boundaries of households, clusters or segments. The purpose of this validation is to ensure that field workers do not inadvertently or deliberately omit eligible households from the data collection process. By conducting this validation, the district supervisors aim to maintain the quality and integrity of the data.A dedicated quality control associate at the data management unit (DMU) will also review pictures of immunization cards which will be taken by survey teams and compare them with the results of the survey to validate the quality of data transcription by data collectors.The CHCs’ performance and refusal rates will be assessed via independent and robust monitoring through independent surveys, data from the National Emergency Operations Centre (NEOC) and Polio Eradication Program data for OPV coverage.To improve the acceptance of the vaccine along with staff performance, stakeholders’ engagement, the performance of community groups, community mobilization sessions and the frequency of individual and group meetings will be monitored.Conditional non-cash need-based incentives will be decided based on reductions in the polio vaccine refusals, PMC and SMC.

## 6. Statistical Analysis

The baseline characteristics of the study population will be reported as frequencies and percentages for categorical variables, and mean, standard deviation (SD) and median interquartile range (IQR) for continuous variables as appropriate. The immunization coverage will be reported overall and according to time and intervention groups. Subgroups including age, gender, maternal years of education, socio-economic status and area of residence will also be compared for immunization coverage. A difference-in-difference (DID) method will be used to estimate the impact of intervention over time. Multivariate analysis will be performed using binary logistic regression at endline to determine the impact of intervention controlling for multiple confounding factors. The analysis will be carried out in STATA version 17 [29].

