### 3.4. Study Setting

The study will be conducted in two intervention and two control HRUCs. There will be one intervention HRUC and one control HRUC, each from a peri-urban district of Karachi and a rural district of Banu, Pakistan. The intervention HRUC of Karachi is Haji Mureed Goth and the control is UC 49 in Nazimabad in the central district, which has an area of 69 km^2^, a population of approximately 2,971,626 and a density of 43,000/km^2^ and is divided into four towns [22]. While the intervention HRUC of Bannu city is Mira Khel and the control is Khwajamad, both of these areas belong to Bannu district, which has a population of 1,210,183 and a density of 610/km^2^ with four tehsils [23]. Both control and intervention UCs were chosen in consultation with the EOC as they have similar demographics and vaccine coverage rates.

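### The regression stated to adjust for confounders uses endline data only, so a baseline gap between the non-randomised arms that its covariates miss is counted as intervention effect

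*Protocol article*

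**What the plan says.** Section 3.2 describes a "pre/post-test quasi-experimental design with two intervention HRUCs and two control HRUCs". For each intervention council, "a separate matched control HRUC of comparable size and location will be included". Section 3.4 adds: "Both control and intervention UCs were chosen in consultation with the EOC as they have similar demographics and vaccine coverage rates". It gives no coverage or refusal figures for any of the four UCs.

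Section 5.2 says that, besides the programme's routine data, "the project team will also collect data at baseline and endline". The survey takes 30 areas of seven households in each UC: 210 interviews per UC and 840 in total.

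Section 6 names two analyses of impact. The first uses both rounds: "A difference-in-difference (DID) method will be used to estimate the impact of intervention over time". No covariates are mentioned for it. The second is adjusted but tied to one time point: "Multivariate analysis will be performed using binary logistic regression at endline to determine the impact of intervention controlling for multiple confounding factors". The confounders are not listed.

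**The concern.** An endline contrast between arms identifies the intervention effect only if the arms, given the covariates, would have had the same outcome without the intervention. Randomisation would support that assumption; here the UCs were chosen. A pre/post design with controls exists so that the assumption is not needed. Yet the one analysis stated to control for confounding leaves the baseline round out.

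Covariates may not close the gap. Section 6 lists age, gender, maternal education, socio-economic status and area of residence as subgroups, and the adjustment set may resemble these. The Introduction attributes refusal to faith, perceptions of safety, mistrust and community resistance. Those act partly at community level, and demographic covariates capture them poorly. The outcome in Section 3.6 is refusal among still missed and persistently missed children. The similarity claimed in Section 3.4 concerns demographics and coverage, not refusals.

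At stake is the credibility of the adjusted result. A reader may take it as the more rigorous of the two because it is adjusted, although it lacks the protection that the design provides.

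**Working it through.** **The plan's own figure.** 4 UCs x 30 areas x 7 households = 840, or 210 per UC. This reproduces. With two UCs per arm, that is 420 households per arm, if 840 is the number per round; Section 5.2 does not say so explicitly. The article states no alpha, power, effect size or baseline rate, so there is no power figure to reproduce. All rates and design effects below are assumptions.

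**Case 1: no true effect; a residual baseline gap persists to endline.** Let p1 and p0 be vaccine acceptance in the intervention and control arms after adjustment.

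- Endline odds ratio: OR = [p1/(1 − p1)] / [p0/(1 − p0)]
- Standard error of the difference: SE = sqrt{deff x [p1(1 − p1) + p0(1 − p0)] / 420}
- False rejection, two-sided 5%: P(|Z + gap/SE| > 1.96)

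For 90% v 85%:

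- OR = (0.90/0.10) / (0.85/0.15) = 9.00/5.67 = 1.59.
- Under independence, SE = sqrt[(0.0900 + 0.1275)/420] = 0.0228 and gap/SE = 2.20, so rejection is about 59%.
- At design effect 2, SE = sqrt[0.2175/210] = 0.0322 and gap/SE = 1.55, so rejection is about 34%.

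The same steps for other gaps:

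| Acceptance, intervention v control | Endline OR | False rejection, deff 1 | False rejection, deff 2 |
|---|---|---|---|
| 90% v 87% | 1.34 | 28% | 16% |
| 90% v 85% | 1.59 | 59% | 34% |
| 80% v 70% | 1.71 | 92% | 66% |

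The design effect changes the rejection rate but not the bias in the odds ratio. In each row an arm x period contrast has expected value 0 percentage points (ratio of odds ratios 1.00), provided trends are parallel.

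**Case 2: a true 50% relative reduction in refusals in the intervention arm; control constant at 10%.** The 50% is borrowed from the 12-month incentive target in Section 4.2.2, for illustration only.

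- Intervention starts at 20% and falls to 10%. Endline OR = (0.10/0.90)/(0.10/0.90) = 1.00, so the effect is hidden. The contrast using both rounds gives (0.10/0.90)/(0.20/0.80) = 0.44.
- Intervention starts at 8% and falls to 4%. Endline OR = (0.04/0.96)/(0.10/0.90) = 0.38. The contrast using both rounds gives (0.04/0.96)/(0.08/0.92) = 0.48, so the endline model exaggerates the effect.

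**Price of using both rounds.** With equal rates and independent samples in the two rounds, the variance of the DID is twice that of the endline contrast. For 90% v 85% under independence, the 95% half-width rises from 1.96 x 0.0228 = 4.5 points to 1.96 x 0.0322 = 6.3 points, a factor of sqrt(2).

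**The case against.** The strongest reply is that the plan does use the baseline. The sentence just before the regression plans a DID, which removes any constant gap, and the same section reports coverage by time and group, so a gap would be visible. This stands. A reader might infer that the study's impact estimate as a whole ignores baseline; the documents do not support that.

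A reader might also infer that every pre-existing difference passes into the odds ratio. It does not. The regression controls for confounders, so only the part they leave unexplained gets through.

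The UCs were matched on size and location and are said to have similar coverage. This lowers the risk, and gaps of 5 or 10 points run against the stated basis of selection. But the claim has no figures, does not mention refusals, and rests on two UCs per arm.

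The article is silent on whether the DID is adjusted, and it does not rank the two analyses. An analysis plan commonly settles both, so neither silence is a fault in itself. The endline restriction is different: the article states the model, the time point and the purpose.

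Finally, the rates are hypothetical, and independence does not fit a 30 x 7 cluster survey. Hence the design-effect-2 figures and the label of illustration.

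**Conclusion.** The point holds in a limited form. The analysis stated to control for confounding is fixed at endline in a non-randomised comparison with two UCs per arm, although baseline data are collected. Any baseline difference that its covariates do not explain enters the odds ratio and can push it in either direction. A residual gap of 90% v 85% gives OR 1.59 with no true effect, and about 59% false rejection under independence or 34% at a design effect of 2, against a nominal 5%. These figures assume the rates shown, a gap that persists to endline, and 840 interviews per round.

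The planned DID and the claimed similarity of the UCs mean that the study's conclusions need not be biased. This is an inexpensive improvement to a stated analysis; the design itself is not invalidated.

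**What to change.** In Section 6, replace the endline restriction with one covariate-adjusted model on the pooled baseline and endline survey records. Include arm, period, arm x period, site (Karachi pair or Bannu pair) and the household covariates, with standard errors that respect the survey clusters. Report the arm x period term, with its confidence interval and on a scale named in advance, as the main adjusted impact estimate. Keep the endline-only regression as supportive or descriptive.

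State two limits alongside it. The estimate relies on parallel trends. And with only two UCs per arm, clustering at the level of the survey areas does not capture differences in trend between whole UCs.

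The cost is a change of wording in Section 6 and a wider interval: variance roughly doubles, so width grows by about 1.4. No new data are needed.
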